**Visit 1 - Day 7**

- A thorough clinical assessment through physical examination and vital signs will be performed.
- Safety assessment (AEs, SAEs, IRTs and check for nephrotoxicity and hepatotoxicity and laboratory values for different parameters) will be done.
- Laboratory investigations done:-Hematology, Renal and Liver function tests, electrolytes as outlined in the screening section.
- Monitoring, recording and reporting for AEs, if any, will be done appropriately.
- Previous and concomitant medications will be recorded.
- DLT assessment will be performed
- The patient will be discharged and asked to return on Day 30. A thorough clinical examination will be done.

**Visit 2- Day 30 (+/- 5 days):**

- A thorough clinical examination will be done.
- Splenic aspirate will be done to assess parasitological cure and will be graded in exactly the same manner as outlined above. The score will be assessed as follows:
  - 1. If the score is 0, then it is concluded as Initial cure achieved. Patient will be followed up till 6 months after study drug administration.
    2. If the score is +1 then repeat confirmatory splenic aspirate at 15^th^ day after Day 30 aspirate (i.e. Day 45 of study)
    3. If the score is above +1, then these patients will be considered as treatment failures and will be discontinued from the study & rescue medication will be given. No further follow‑up will be performed.
- Prothrombin time will have to be carried out before splenic aspiration and procedure will be done only if result is ≤4 seconds above the control
- Safety assessment (AEs, SAEs, IRTs, nephrotoxicity hepatotoxicity and laboratory values for different parameters) will be done
- Laboratory investigations done:-Hematology, Renal and Liver function tests, electrolytes as outlined in the screening section
- Vital signs will be recorded.
- Monitoring, recording and reporting for AEs, if any, will be done appropriately.
- Previous and concomitant medications will be recorded.
- Other laboratory investigations can be done, at the investigator’s discretion.

**Visit 2 - Day 45 (Additional Visit, +/-5 days):**

- This visit will be done only for those patients who did not have complete parasitological cure on Day 30 and had a splenic aspirate score of +1. If the score is +1 and above, the patients will be considered as treatment failures and will be discontinued from the study and given rescue medication as deemed fit by the Investigator.
- A thorough clinical examination will be done.
- Splenic aspirate will be done to assess parasitological clearance. The score will be assessed as follows :

1. If the score is 0, then it is concluded as initial cure achieved. Patient will be followed up till 6 months after study drug administration.
2. If the score is +1 or above, then these patients will be considered as treatment failures and will be discontinued from the study and rescue medication will be given. No further follow-up will be performed.

- Prothrombin time will have to be carried out before splenic aspiration and procedure will be done only if result is ≤4 seconds above the control.
- Vital signs will be recorded.
- Patients who have parasitological clearance on Day 30 will not visit on Day 45.
- Laboratory investigations done:-Hematology, Renal and Liver function tests, electrolytes at investigator’s discretion.
- Monitoring, recording and reporting for AEs, if any, will be done appropriately.
- Previous and concomitant medications will be recorded.

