**Visit 3 (End of study [EOS] visit- 6 months after study drug administration) (-2 weeks to +4 weeks):**

- Thorough clinical examination will be done
- Vital signs will be recorded
- Safety assessment (AEs, SAEs, IRTs and check for nephrotoxicity and hepatotoxicity and laboratory values for different parameters) will be done
- Laboratory investigations will be done:-Hematology, Renal and Liver function tests, electrolytes as outlined in the screening section
- Splenic aspirate will be done to assess parasitological cure only in patients in whom a relapse of the illness is indicated, in others only clinical assessment will be done to define definitive cure at 6 months (Prothrombin time will have to be carried out before splenic aspiration and procedure will be done only if result is ≤4 seconds above the control)
- Monitoring, recording and reporting for AEs
- Previous and concomitant medications will be recorded.

Criteria for Efficacy and Safety Evaluation:

**Efficacy:** Patients will be assessed for initial cure on the basis of splenic aspirate score on Day 30 after first dose of study drug as follows:

| **Splenic aspirate score** | **Interpretation and action to be taken** |
| --- | --- |
| 0 | At Day 30:  Initial cure achieved; Follow-up till 6 months after study drug administration |
| +1 | Repeat confirmatory splenic aspirate at 15^th^ day after Day 30 aspirate (i.e. Day 45 of study)  At Day 45:  0 ‑ Initial cure achieved, follow-up till 6 months after study drug administration.  1+ and above - The patients will be considered as treatment failures. The patients will be withdrawn from study and given rescue medication as deemed fit by the PI. |
| Above +1 | At Day 30:  These patients will be considered as treatment failures and will be discontinued from the study and given rescue medication as deemed fit by the PI. |

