## Patient Completion and Withdrawal

### For each patient, according to the protocol, the study is deemed

- **Completed**

The patient will be administered study treatment as per the protocol, and completes all the safety and efficacy assessments on- Day 7, Day 30, Day 45 (only for patients with splenic aspirate score +1 on Day 30), and at 6 months after study drug administration.

- **Discontinued/withdrawn**- Withdrawal from the study can occur under the following circumstances:
  - 1. Death
    2. Adverse event
    3. Lack of efficacy (treatment failure)
    4. Patient consent withdrawal
    5. Investigator’s discretion
    6. Sponsor’s decision
    7. Pregnancy in a patient
    8. Lost to follow-up*

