### Recording Patient Withdrawals

In the event of a patient withdrawal, the following information must be recorded in the CRF:

- Date of withdrawal
- Reason for withdrawal
- Last treatment date
- Follow-up assessments

If a patient withdraws or is withdrawn from the study, he/she will be requested to return for a follow-up visit after 1 week of the withdrawal date, for recording AEs and physical examination.

The Investigator should continue to follow-up all SAEs or other AEs that are considered to be related to the study drugs, until resolved or assessed to be chronic or stable by the Investigator. This should be documented in the patient’s medical records. This follow‑up may be extended beyond the end of the study period.

In the case of patients lost to follow-up, all attempts to contact the patient must be documented in the patient’s medical records.

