# 17. ASSESSMENT OF EFFICACY

**Efficacy:** Patients will be assessed for initial cure on the basis of splenic aspirate score at Day 30 after first dose of the study drug as follows:

| **Splenic aspirate score** | **Interpretation and action to be taken** |
| --- | --- |
| 0 | At Day 30:  Initial cure achieved; Follow-up till 6 months after study drug administration |
| +1 | At Day 30:  Repeat confirmatory splenic aspirate will be done at 15^th^ day after Day 30 aspirate (i.e. Day 45 of study)  At Day 45:  0 ‑ Initial cure achieved, follow-up till 6 months after study drug administration  1+ and above - The patient will be considered as treatment failure and will be withdrawn from study and given rescue medication as deemed fit by the PI. No further follow-up will be performed. |
| above +1 | At Day 30:  These patients will be considered as treatment failures and will be discontinued from the study and given rescue medication as deemed fit by the PI. |

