## Efficacy evaluation

- Patient will be considered eligible for efficacy evaluation if study drug has been administered and at least one efficacy assessment has been done.
- Failure of treatment is defined as the presence of any of the following conditions:

Presence of amastigotes on splenic smear examination

Treatment discontinuation due to intolerance

- Patients who discontinued the study drug before completing the total dosage due to a DLT will be considered non-evaluable.
- Non-evaluable patients who receive any dose of study drug will be included in the safety analysis.

Clinical status will be graded on a daily basis until the patient is hospitalized and at each visit thereafter.

- - - Timing of assessments: (applying the criteria for efficacy endpoint)

First assessment will be done at Day 30 after study drug administration

Second assessment on Day 45 ‑(only for patients who have a splenic aspirate score of +1 on Day 30) if the splenic score is 0, follow-up will be performed at 6 months after study drug administration and if the splenic score is +1 and above, no further follow-up will be performed.

If the splenic score is above +1 on Day 30 or Day 45 patient will be a treatment failure and no further follow-up will be performed.

At the end of 6 months after study drug administration, only if relapse is suspected – EOS visit.

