# 18. ASSESSMENT OF SAFETY

The recording of AEs is an important aspect of study documentation. It is of utmost importance that all staff members at the site involved in the study are familiar with the content of this section in order to document all AEs according to the detailed guidelines set out below.

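### Sections 13 and 17 end all follow-up of parasitological failures without limiting this to efficacy, which taken literally contradicts the adverse-event follow-up rules for withdrawn patients

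*Protocol*

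**What the plan says.** **Instructions that stop follow-up**

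- Section 13, Visit 2, Day 30: a patient with a score above +1 is a treatment failure and is "discontinued from the study & rescue medication will be given. No further" follow-up is to take place.
- Section 13, Visit 2, Day 45: for a score of +1 or above, "rescue medication will be given. No further follow-up will be performed".
- Section 17, efficacy table, Day 45 row: the patient is withdrawn and "given rescue medication as deemed fit by the PI. No further follow-up will be performed".
- Section 17.2, timing of assessments: with a score above +1, the "patient will be a treatment failure and no further follow-up will be performed". The sentence before it says the same of +1 and above at Day 45.

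**Rules that continue it**

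- Section 12.6.1 lists "Lack of efficacy (treatment failure" among the reasons for withdrawal.
- Section 12.6.3, on any patient who withdraws or is withdrawn: "he/she will be requested to return for a follow-up visit after 1 week of the withdrawal date, for recording AEs and physical examination". It also has SAEs and drug-related AEs followed until they resolve or are judged chronic or stable, beyond the end of the study if need be.
- Sections 18.2.3 and 18.3.5: a withdrawn patient with an AE present is re-evaluated within two weeks, with more follow-up if it has not resolved.

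The Study Summary gives the Day 45 failure instruction without the stopping phrase: "The patients will be withdrawn from study and given rescue medication as deemed fit by the PI". The Day 30 row of the section 17 table also omits it.

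**The concern.** The same patient, a parasitological failure at Day 30 or Day 45, is told to have no more follow-up in one part of the protocol and is called back for AEs in another. Section 13 is the visit-by-visit instruction that site staff carry out, so the stopping phrase is the one most likely to be acted on.

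What is at stake is safety information and patient care after failure. These patients are about to receive a second antileishmanial course. Under section 16.2 this may be AmBisome 5 mg/kg on Days 1, 3, 5 and 7. An AE open at discontinuation, or one that appears soon afterwards, would have no planned contact. Section 20.2.3 tabulates AEs and SAEs in all dosed patients, so recording after Day 30 or Day 45 would depend on the efficacy result.

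**Working it through.** No sample size, power or rate enters here. The check is a comparison of texts, plus one sum for the rescue dose.

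**Step 1: do the withdrawal rules cover these patients?** Yes. Section 12.6.1 names treatment failure as a withdrawal reason, and sections 13 and 17 discontinue or withdraw the patient. Sections 12.6.3, 18.2.3 and 18.3.5 make no exception for failures.

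**Step 2: the instructions side by side**

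| Source | Instruction for a Day 30 or Day 45 failure |
|---|---|
| 13 (Day 30 and Day 45), 17 (Day 45 row), 17.2 | No more follow-up, type not stated |
| 12.6.3 | Return after 1 week for AEs and physical examination; SAEs and related AEs followed until resolved, chronic or stable |
| 18.2.3, 18.3.5 | Re-evaluation within 2 weeks if an AE is present, then more if unresolved |

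Taken literally, the first row excludes the other two.

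**Step 3: does section 13 itself limit the phrase to efficacy?** Not expressly. In both visit lists the opposite branch, a score of 0, sends the patient to follow-up until 6 months. That leads to Visit 3, which includes a safety assessment, laboratory tests and AE recording as well as the cure assessment. So the follow-up being switched off is not purely an efficacy activity. Section 12.6.3 also calls its AE visit a follow-up visit, and section 18.2.3 uses the same term in its title. Nothing tells a site that the word means something narrower in section 13.

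**Step 4: is there a precedence rule?** The opening of section 18 asks staff to know that section "in order to document all AEs according to the detailed guidelines set out below". It points them to the AE rules but does not say that those rules override a visit instruction.

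**Step 5: exposure in the uncovered period.** If AmBisome is chosen as rescue: 4 infusions × 5 mg/kg = 20 mg/kg, after the single 15 mg/kg study dose. The investigator may choose another drug instead.

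**Step 6: what is not touched**

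- Definitive cure: these patients are already failures.
- Dose-limiting toxicities: assessed to Day 7.
- Infusion-related toxicities: tied to the Day 1 infusion.
- Day 7 and Day 30 safety assessments: done by the time failure is declared.

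**Step 7: effect on the arm comparison.** The instruction is the same in both arms. If the share of failures with a missed first AE is also the same, any distortion is proportional to the difference in Day 30/45 failure rates. The protocol gives neither quantity, so no figure is offered.

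**The case against.** The strongest answer is that context already limits the phrase to efficacy. In section 17.2 it stands under a heading on applying the efficacy criteria, and one sentence sets it against the 6-month follow-up of patients with a score of 0. In section 13 it is an outcome under the splenic-score list, while AE monitoring is a separate bullet of the same visit. Sections 12.6.3 and 18 are specific rules for withdrawn patients, and a careful site could follow both sets. The summary's omission of the phrase fits that reading too.

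Much of this stands: the efficacy-only reading is plausible and is probably what was intended. But the protocol never states it, the opposite branch leads to a visit that includes safety work, and no precedence rule settles the matter.

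Four stronger readings are tempting, and the documents do not support them:

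- **A gap in SAE reporting.** A reader might infer this from section 18.4, where the reference to the course of the study concerns treating an SAE. The reporting bullets there carry no such limit.
- **A lost 6-month safety visit.** The score rules send only patients with a score of 0 to 6 months. The sentence in section 18.3.1 on recording AEs to the end-of-study visit after withdrawal is garbled, and section 18.2.2 is ambiguous for early withdrawals. Neither is relied on.
- **A clash between one week and two weeks.** A one-week visit satisfies a two-week limit.
- **Bias in the efficacy result.** There is none, as these patients already count as failures.

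**Conclusion.** The point holds as a minor defect of wording: four places state an unqualified stop to follow-up that, taken literally, contradicts sections 12.6.3, 18.2.3 and 18.3.5 for the same patients. The practical loss, if a site acts on the literal text, is the one-week AE visit, the re-evaluation of any open AE, and continued follow-up of SAEs and related AEs, at a time when rescue has just begun. This assumes that at least some sites follow section 13 as written. It is confined to parasitological failures at Day 30 or Day 45, and its size between arms cannot be stated from the protocol.

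**What to change.** In section 13 (Day 30, score above +1; Day 45, score +1 or above), in the Day 45 row of the section 17 table, and at both occurrences in section 17.2, replace the phrase with: *No further efficacy follow-up will be performed; AE follow-up continues as in sections 12.6.3 and 18.*

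The cost is a wording amendment in four places and a few AE contacts with patients who failed treatment. Those contacts are already required by sections 12.6.3, 18.2.3 and 18.3.5. Design, sample size and efficacy analysis do not change.

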**Visit 3 - End of study visit- 6 months after study drug administration (-2 weeks to +4 weeks):**

- A thorough clinical examination will be done.
- Safety assessment (AEs, SAEs, IRTs, check for nephrotoxicity and hepatotoxicity and laboratory values for different parameters) will be done
  - Laboratory investigations will be done:-Hematology, Renal and Liver function tests, electrolytes as outlined in the screening section.
- Splenic aspirate will be done to assess parasitological cure in patients in whom a relapse of the illness is indicated by recurrence of fever, splenic enlargement. In others, only clinical assessment will be done to define definitive cure at 6 months.
- Prothrombin time will have to be carried out before splenic aspiration and procedure will be done only if result is ≤ 4 seconds above the control
- Definitive cure will be defined as initial cure at Day 30 or 45 followed by absence of clinical signs and symptoms of relapse of Kala-azar till 6 months after study drug administration. If clinical signs and symptoms of relapse of the disease is suspected at any time during the 6 month follow up, splenic aspirate shall be done at 6 months or earlier after study drug administration.
- Vital signs will be recorded.
- Monitoring, recording and reporting for AEs, if any, will be done appropriately
- Previous and concomitant medications will be recorded.

**Study Treatment Interruption:**

- In case of any episode of intolerable toxicity or abnormal laboratory findings temporary discontinuation of the study drug as judged by the investigator will be allowed.
- In the event of any emerging complication or deterioration, all possible measures will be taken to safeguard the health and life of a patient, notwithstanding the possibility of dropout from the study.

**DLTs during the study:**

- Recruitment of all subsequent patients in any dosage regimen will be stopped or discontinued if the overall percentage of patients in the study with DLT is >33%. This criterion will only be applicable after randomization of 25^th^ patient in either arm.
- DLT of the study drugs for this study is defined as:

i) Any drug related grade III or higher AE classified as nephrotoxicity/ hepatotoxicity evaluated as per NCI-CTC-AE-v3).

ii) Any other drug related grade IV or higher toxicity except hematological toxicity (evaluated as per NCI-CTC-AE-v3).

iii) If patient’s hematological parameter is in CTC grade III or grade IV at baseline, then a DLT would be considered if there is reduction of ≥33% from baseline.

iv) If patient’s hematological parameter is within normal range or is in CTC grade I or CTC grade II at baseline, then a DLT would be considered if the parameter drops to grade IV or higher

- All the patients will be assessed for DLT up to Day 7 after the administration of first dose of the study drug.

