## 11.5 Study Duration, Treatment Interruption and Termination

The clinical part of the study will start after the approval of the responsible IRB/IEC and after the site initiation visit is performed.

The timeframes of the study will be as follows:

- Total duration of the Clinical study: 1 year 8 months
- Total Clinical Duration (maximum) per patient: 7 months
- Recruitment Period (all patients): 7 months
  - - - **Study Treatment Interruption:**
- In case of infusion related reactions temporary discontinuation of the infusion or administration of concomitant medications as judged appropriate by the investigator, (other than prohibited medications) will be permitted.
- None of the patients will be replaced.

**The entire study may be prematurely terminated/discontinued** if there is,

- Comprehensive deficiency in the recorded data or protocol compliance so that the results of the study cannot be reliably assessed.
- The Sponsor, PI(s) and the Project Manager, if appropriate commonly decide premature termination, after consultation with the Ethics Committee and the study sponsor.

In the event of early termination, PI(s) will cease use of the IP immediately. All outstanding Case Report Forms (CRFs) will be completed and returned to SIRO together with completed drug inventory, records and remaining trial material.

A written statement fully documenting the reasons for such a termination will be provided from Bharat Serums and Vaccines Ltd. to the IRB/IEC and Drugs Controller General of India (DCGI).

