## Randomization and Blinding

- Since this is an open label study, blinding is not applicable.
- Permuted Block randomization schedule with block of size 4 and ratio of 3:1 in the two groups (Amphomul and AmBisome) will be generated for each center.
- Treatment with IP/Comparator drug will begin only after successful screening (signing informed consent and fulfillment of all eligibility criteria).
- After meeting eligibility criteria, the patient will sequentially be allotted to unique subject ID and treatment as per randomization schedule for that center.
- A separate screening and enrolment log will be maintained.
- Neither the Investigators nor patient/patient’s LAR will be blinded to the treatment regimen.

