## Dosing schedule and Administration

### Investigational product (Amphomul^®^)

- Amphomul^®^ shall be administered by IV route at the site of appropriate IV access. It can also be administered into the central venous catheters, if appropriate. The drug should be administered as a slow IV infusion.
- The Investigator or designee will be required to withdraw Amphomul^®^ from the vial(s), and administer each patient the dose specified as slow IV infusion.
- Before administration, Amphomul^®^ will be diluted to 1 mg/mL in 5% dextrose.
- Test dose consisting of 1 mg will be administered in 5% dextrose over a period of approximately 15-20 minutes prior to administration of full-dose infusion of Amphomul^®^.
- The IP (Amphomul^®^)*,* diluted (maximum dilution allowed to 1 mg/mL) in 5% dextrose will be administered as a slow IV infusion over 4 to 6 hours.
- As for use of all Amphotericin B products, facilities for cardiopulmonary resuscitation will be kept readily at hand when administering the drug due to possible occurrence of anaphylactic reactions.
- The patients will be observed for 6 hours following the end of infusion, with appropriate medical treatment readily available in case of a rare anaphylactic reaction during the administration of infusion. Reactions that occur during this time must be recorded by the Investigator in the CRF.
- In case of any toxicity due to study drug, patient will be withdrawn from the study as per investigator’s discretion

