## Reporting of SAEs

- Any SAE occurring during the course of the study should be treated by established standards of care to protect the life and health of the patient.
- If such treatment constitutes a significant deviation from the protocol, the Investigator should notify SIRO immediately to determine whether the patient should be dropped out from the study.
- Any SAE, irrespective of causality, must be **immediately** notified to the safety team at SIRO Clinpharm Pvt. Ltd. **by telephone ([contact], 24 hour*‑*contact - [name]).**
- This must be followed up **within 24 hours by facsimile *(+*[name]*)*** on the study specific SAE reporting form with as much detailed information regarding the event that is available.
- Investigators should not wait to receive additional information to fully document the event, before notifying SIRO of a SAE.
- The SAE reporting form should detail all relevant aspects of the AEs in question. Where applicable, information from relevant hospital case records and autopsy reports should be obtained and provided, in a blinded fashion, to SIRO.
- All SAEs should be reported within 24 hours to SIRO and, within 7 calendar days to IRB/IEC on Investigator’s knowledge of the event. Confirmation of submission to the IRB/IEC must be forwarded to SIRO.
- The event must also be recorded on the CRF AE page.

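### The only numeric safety stop pools DLTs over both arms at 3:1, so at a given look Amphomul's observed DLT rate can be well above 33% (up to 44% if AmBisome has none) without triggering it

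*Protocol*

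**What the plan says.** The stopping rule appears in Section 8 (Assessment of Dose Limiting Toxicity) and again in Section 13 (DLTs during the study). Recruitment to either regimen stops "if the overall percentage of patients in the study with DLT is >33" per cent, and the criterion starts to apply once the 25th patient in either arm has been randomised. DLTs are collected for everyone over the first week: "All the patients will be assessed for DLT up to Day 7 after the administration of first dose of the study drug".

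Section 15.3 fixes the allocation, "Permuted Block randomization schedule with block of size 4 and ratio of 3:1 in the two groups", with a separate schedule for each centre. It also states "Since this is an open label study, blinding is not applicable". Section 11.2 plans 375 Amphomul and 125 AmBisome patients.

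The other safety provisions carry no numeric limit for an arm:

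- Section 11.5 lets the sponsor, investigators and project manager "commonly decide premature termination, after consultation with the Ethics Committee and the study sponsor".
- Section 13 (Study Treatment Interruption) says "temporary discontinuation of the study drug as judged by the investigator will be allowed".
- Section 15.6.1 says "In case of any toxicity due to study drug, patient will be withdrawn from the study", at the investigator's discretion.
- Section 18.4 says "All SAEs should be reported within 24 hours to SIRO and, within 7 calendar days to IRB/IEC".
- Section 18.5 sends serious, unexpected, at least possibly related events to the regulator and the ethics committees within 7 or 14 days.

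**The concern.** The rule's wording sets one denominator, all patients in the study. The references to any regimen and to either arm say whose recruitment stops and when the rule begins. They do not create a percentage for each arm.

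A well-tolerated comparator therefore dilutes a toxicity signal from the product under test. The rule is least sensitive where a numeric stop is most needed, when Amphomul is toxic and AmBisome is not. At stake is how many patients, some as young as 5, receive a single 15 mg/kg infusion of Amphomul before recruitment is halted. Pooling is not needed to protect a blind, because the trial is open label and DLTs are known by arm.

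**Working it through.** **Inputs.** Threshold above 33% of all patients (Sections 8 and 13). Weights 0.75 and 0.25 (3:1 in blocks of 4, Section 15.3). Enrolment 375 + 125 (Section 11.2), which agrees with the plan's own inflation: 300/0.8 = 375, 100/0.8 = 125, 400/0.8 = 500. The protocol states no DLT rate for either arm and no operating characteristics for the rule, so all rates below are assumptions.

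**Largest observed Amphomul rate with no stop.** There is no stop while 0.75·pA + 0.25·pB ≤ 0.33, so pA ≤ (0.33 − 0.25·pB)/0.75.

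| Observed AmBisome rate | Largest Amphomul rate without a stop |
|---|---|
| 0% | 0.3300/0.75 = 44.0% |
| 5% | 0.3175/0.75 = 42.3% |
| 10% | 0.3050/0.75 = 40.7% |
| 20% | 0.2800/0.75 = 37.3% |

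Check in whole patients with no AmBisome DLTs: 33 of 100 is 33.0%, no stop, yet 33/75 = 44.0% on Amphomul. At full enrolment 165/500 = 33.0%, no stop, yet 165/375 = 44.0%. At the earliest look of 25 + 8 patients the ceiling is lower: 11/33 = 33.3% stops and 10/33 = 30.3% does not, so the most is 10/25 = 40%.

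**One look, exact binomial, true rates 40% and 5%.**

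| Patients | Pooled rule | Amphomul alone above 33% |
|---|---|---|
| 25 + 8 | 11 or more of 33: 0.48 | 9 or more of 25: 0.73 |
| 75 + 25 | 34 or more of 100: 0.30 | 25 or more of 75: 0.90 |
| 375 + 125 | 0.17 | 0.998 |

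The true pooled rate is 0.75 × 0.40 + 0.25 × 0.05 = 0.3125, below the limit, so at a single look more data make a pooled stop less likely.

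**Repeated looks, simulation.** 20,000 trials of 500 patients in blocks of 4. The pooled rule is active once either arm has 25 patients and is checked after every patient. The modified rule adds Amphomul alone above 33% at 100, 200, 300 and 400 patients. The Day 7 lag is ignored. Mean Amphomul exposure counts 375 when there is no stop.

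| True rates, Amphomul/AmBisome | Stop, pooled rule now | Stop, with the added criterion |
|---|---|---|
| 40%/5% | 0.78 (mean 118 Amphomul patients) | 1.00 (mean 53) |
| 40%/10% | 0.88 | 1.00 |
| 40%/20% | 0.98 | 1.00 |
| 20%/20% | 0.07 | 0.07 |
| 25%/25% | 0.27 | 0.29 |

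If the pooled rule were checked only at 100, 200, 300 and 400 patients, it would stop 0.45 of trials at 40%/5%.

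**The case against.** Several objections have force.

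- A reader might infer that the rule tolerates a true Amphomul DLT rate of 44%. It does not. The 44% is an observed rate at one look. The protocol gives no look schedule, and if the rule is checked after every patient, chance excursions trigger it often: true rates of 44%/0% stop about 0.91 of trials. At 50%/5% it stops essentially all of them, after about 30 Amphomul patients on average.
- A reader might infer that pooling has no benefit. It does: it spares the trial false halts driven by the small AmBisome arm. That is why the fix below leaves that arm out.
- The harmful scenario is assumed. Section 9.6 reports no clinically recognisable hepatic or renal disturbance with the single 15 mg/kg dose in Phase II, and both arms receive the same active drug at the same dose. Haematological DLTs need not be judged drug related, so they can arise in either arm. If AmBisome's rate is near 20%, the gap almost vanishes. This limits the size of the concern. A stopping rule nevertheless exists for results that differ from earlier experience.
- Other safeguards remain: hospital stay and DLT assessment to Day 7, SAE reports within 24 hours, expedited reports to the regulator and ethics committees, and joint discretionary termination. They reduce the consequence, but none supplies a numeric limit for the test arm.

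**Conclusion.** The point holds as a weakness in design. The pooled denominator lets Amphomul's observed DLT rate lie between 37.3% and 44.0% at a given look without a stop, for AmBisome rates from 20% down to 0%. At assumed true rates of 40%/5%, about 22% of trials (1 − 0.78) would never stop under the pooled rule even with a check after every patient.

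The ceilings need only the threshold and exact 3:1 allocation. The stopping probabilities also rest on assumed DLT rates and an assumed look schedule.

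A reader might go further and call the rule self-contradictory, or say that an Amphomul rate above 33% breaches the protocol. The text does not support that: it sets no limit within an arm, so nothing stated is breached. The primary result, sample size and efficacy analysis are unaffected.

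**What to change.** In Sections 8 and 13, keep the pooled criterion and add: the same limit of more than 33% applies to the Amphomul arm alone, checked when 100, 200, 300 and 400 patients have been assessed to Day 7. If it is met, recruitment to the whole study halts pending sponsor and safety review, so that one arm is not closed alone. The threshold itself stays a matter for the sponsor's physicians.

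The cost is wording in two sections, since Day 7 DLT data are already collected and known by arm. With equal true rates in both arms, the chance of a false halt goes from about 0.07 to about 0.07 at 20%, and from 0.27 to 0.29 at 25%. Adding the AmBisome arm as well would raise these to about 0.11 and 0.40, so that is not recommended.
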